### Study outcomes

The primary outcome is the first running-related injury occurring during the follow-up and defined as any running-related physical complaint in the lower limbs or lower back region that causes a restriction on or stoppage of running (distance, speed, duration or training) for at least 7 days. Practically, this corresponds to injury forms where the participant answered options (c) or (d) in question 1 or options (b), (c) or (d) in question 2 or question 3 of the OSTRC-O questionnaire.^27^ Injury duration will be computed as the days between the date of injury or symptom onset and the date of return to full participation reported in our electronic system (via a dedicated form). Secondary outcomes are as follows: (1) first running-related physical complaint in the lower limbs or lower back region that causes a restriction on or stoppage of running (distance, speed, duration or training) for at least 1 day (ie, injury forms with options (c) or (d) in question 1 or options (b), (c) or (d) in question 2 or question 3 of the OSTRC-O questionnaire, without any minimal duration), (2) first physical complaint including pain, ache, joint instability, stiffness or any other complaint resulting from participating in running activities, including but irrespective of the need of medical attention or time-loss (ie, injury forms with option (b) in question 1 of the OSTRC questionnaire will also be considered), (3) first substantial running-related injury (ie, injury forms where the participant answered options (c) or (d) in question 2 or question 3 of the OSTRC-O questionnaire) and (4) first overuse running-related injury (ie, injury forms where the participant answered option (a) in question 10 will be excluded).

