### Data collection

Participants must fill in a baseline questionnaire to collect information regarding sociodemographic characteristics, running experience, training habits, running competitions performed and injury history. The intervention period will start as soon as the participants receive their study shoes and will last 6 months. During this intervention period, the participants are required to use the study shoes for all their running activities, to continue their usual training or follow their planned schedule and to fill out the weekly questionnaire on musculoskeletal problems, as well as on the use of the study shoes during the follow-up. Data on running practice will be downloaded from sports watches and their respective app via Strava in our dedicated electronic system. The system will collect the daily step count via Google Fit and the Apple Health mobile app. Information on using the study shoes will be collected via a weekly questionnaire. Data on cushioning perception will be collected three times using a dedicated questionnaire distributed when the runner has cumulated 5 hours and 25 hours of running and at the end of the intervention, respectively (online supplemental material 3).

Participants will be asked to complete a weekly questionnaire on any problem in the lower limbs or lower back region experienced during the previous 7 days (the Oslo Sports Trauma Research Centre (OSTRC) Overuse Injury Questionnaire).^27^ On top of the four basic questions, information regarding the following is required: date of symptom onset, sports discipline, anatomical location, type of injury, recurrence (ie, new, recurrent, exacerbation or subsequent injury), mode of onset and estimated return date to full participation (online supplemental material 4). Individual e-mail reminders will be sent to the participants who do not complete a weekly questionnaire. Personal phone calls will be made to participants who do not react to the e-mail reminders and if the reported information in the injury form is inconsistent. Study participation will be terminated, and the participant will be right-censored if he/she does not fill in the weekly injury form for two consecutive weeks, does not reply (or react) to the automatic reminders and cannot be reached by phone by the research team.

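### The substantial-injury outcome leaves out question 1, so a form that shows stoppage only through option 1(d) meets the primary outcome's answer criteria but is not counted as substantial

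*Protocol article*

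**What the plan says.** All the outcome rules are in the Study outcomes section of the protocol article.

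- **Primary outcome.** It is a running-related complaint that "causes a restriction on or stoppage of running (distance, speed, duration or training) for at least 7 days". The derivation accepts forms on which the runner "answered options (c) or (d) in question 1 or options (b), (c) or (d) in question 2 or question 3 of the OSTRC-O questionnaire".
- **Secondary outcome 1.** It uses the same answers with no minimum duration: "injury forms with options (c) or (d) in question 1 or options (b), (c) or (d) in question 2 or question 3".
- **Secondary outcome 2.** It widens the net to any complaint, whether or not running time was lost: "injury forms with option (b) in question 1 of the OSTRC questionnaire will also be considered".
- **Secondary outcome 3.** It is the "first substantial running-related injury (ie, injury forms where the participant answered options (c) or (d) in question 2 or question 3". No answer to question 1 leads into it.

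The Data collection section says that the questionnaire has four basic questions plus additional items. It provides for a phone call "if the reported information in the injury form is inconsistent". The form itself is in a supplement that is not shown.

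**The concern.** Two of the rules treat question 1 as a sufficient sign of time loss, and the rule for substantial injury ignores it. The protocol's own use of the options suggests that question 1 rises in severity. Option (b) is brought in only for complaints that need not cost running time, while (c) and (d) stand for restricted or stopped running. It is a fair inference that (d) is the stoppage answer.

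If so, a week in which the runner did not run at all could be recorded through 1(d) alone and be left out of the substantial category, while a week of partial limitation recorded as 2(c) is included. The Statistics section computes incidence and weekly prevalence for each outcome, so both could be understated for this one. Any Fine-Gray comparison of shoes on this outcome could miss or delay some first events.

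**Working it through.** **1. The rules side by side** (all from Study outcomes)

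| Outcome | Question 1 | Question 2 or 3 | Minimum duration |
|---|---|---|---|
| Primary | (c), (d) | (b), (c), (d) | 7 days |
| Secondary 1 | (c), (d) | (b), (c), (d) | none (at least 1 day) |
| Secondary 2 | (b) added | as above | none |
| Secondary 3, substantial | not used | (c), (d) | none stated |

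From secondary 1 to secondary 3 the threshold on questions 2 and 3 moves up from (b) to (c). On question 1 it does not move from (c) to (d); the route disappears.

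**2. Counting answer patterns with 1(d)**

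Assumption: questions 1 to 3 each have options (a) to (d). The article names (b), (c) and (d); (a) is inferred.

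- Complete forms with 1(d): 4 × 4 = 16.
- Failing the substantial rule: questions 2 and 3 must both be (a) or (b), so 2 × 2 = 4 patterns: (a,a), (a,b), (b,a), (b,b).
- Passing it: 16 − 4 = 12.
- Meeting the primary outcome's answer criteria: all 16, because 1(d) is enough.
- A form with 1(d) and questions 2 and 3 both blank fails the substantial rule and meets the primary answer criteria.
- A form with 1(c), 2(c) and 3(a) passes the substantial rule.

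With 1(d) added to the rule, all 16 complete patterns and the blank form would qualify.

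**3. Is the question 1 route redundant?**

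The primary rule joins its routes by *or*. If every form with 1(c) or 1(d) also carried at least (b) in question 2 or 3, the question 1 route would add nothing. Yet the authors write it into both the primary outcome and secondary outcome 1. That suggests they allow for forms that show time loss through question 1 alone. It does not prove that such forms occur.

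**4. Can a power loss be computed?**

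The only sizing is for the primary hypothesis (Sample size section), and it reproduces. By Schoenfeld's formula with HR 1.50, two-sided 5% and 80% power, 191 events are needed. Then 191 / 0.30 = 637 runners for one pairwise comparison, and 637 / 0.90 = 708 after drop-out. That is 354 per group and 3 × 354 = 1062 in total, against the stated 1068.

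The 30% rate in that calculation is the average injury rate used for the primary hypothesis. No event rate, effect size or power is stated for substantial injury. The article also gives no share of forms that would carry 1(d) without (c) or (d) elsewhere. Both inputs for a power figure are missing, so none is given.

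**The case against.** The strongest reply is that the harm depends on a form nobody can see here. The article does not print the option wording and does not say that questions 2 and 3 are skipped after 1(d). If they are always asked, a runner who has stopped would be expected to choose (c) or (d) in at least one, and the form would count as substantial that same week. The four failing complete patterns require a stopped runner to give (a) or (b) on both questions, which is plausibly the kind of form that prompts the call for inconsistent information. A condensed article also commonly leaves form routing to the full protocol.

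Much of this stands. The loss is conditional and may be nil. Two things remain. The rule is stated, not omitted, and it differs from its neighbours without explanation. The call for inconsistent forms does not clearly reach a form with 1(d) and questions 2 and 3 unanswered, which need not look inconsistent.

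A reader might go further and infer that the rule ranks full stoppage below partial reduction, that stopped runners are never counted, or that the comparison loses a definite amount of power. The document supports none of these. Most complete 1(d) patterns qualify, and a runner missed one week may qualify on a later form, which delays the event and does not remove it. Nor does the article present its outcomes as a severity ladder: the list includes any complaint and overuse injury, and nothing is called the most severe.

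**Conclusion.** The point holds as an inconsistency in one secondary outcome. As printed, a form reporting stoppage only through 1(d) satisfies the primary outcome's answer criteria but not the substantial rule, while a form with 1(c) and 2(c) is substantial.

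This rests on reading 1(d) as the stoppage answer, which is inferred from how the protocol uses the options. The practical size is unknown, with a lower bound of zero. It would matter most if questions 2 and 3 are skipped or left blank after 1(d), and little or not at all if they are always answered. The primary outcome, secondary outcomes 1 and 2 and the sample size are untouched.

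**What to change.** Define substantial injury as 1(d), or (c) or (d) in either of questions 2 and 3. Use the same rule for incidence, weekly prevalence and any Fine-Gray model fitted to this outcome. State also whether questions 2 and 3 are asked after 1(d).

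The cost is one clause in the definition and one condition in the derivation code. Question 1 is already collected every week. The Stratified randomisation section keeps the shoe code closed until the analysis is complete, so the change can be made and dated while blinded. If 1(d) is always followed by (c) or (d) in question 2 or 3, the new clause reclassifies no form and does no harm.

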### Sample size

A sample size calculation for Cox regression was used to determine the number of participants needed for the study’s primary hypothesis. With an alpha of 0.05 and a power of 80%, an average injury rate of 30%,^28 29^ an expected HR=1.50 between groups, 33% of participants randomised to each shoe group and an expected drop-out rate of 10%, the total number of participants required is 1068 (ie, 356 participants per group).

### Statistics

Descriptive statistics will be presented as mean and SD for normally distributed continuous variables, median and range for skewed continuous variables, and count and percentage for categorical data, respectively. Shock absorption properties of the three shoe versions will be compared using an analysis of variance while considering the measurement uncertainty of the mechanical test.

Injury incidence will be computed for each outcome as the number of injuries per 1000 hours of running exposure. Injury prevalence will be computed for each outcome and per week by dividing the number of participants who reported an injury by the number of respondents of that week. Average weekly prevalence will be calculated separately for each outcome for the main anatomic locations.

To investigate the effect of shoe version, body mass and other possible risk factors on injury risk, subdistribution HR (sHR) with 95% CIs for the event of interest will be calculated using Fine-Gray models to account for competing risk. The date of inclusion and date of injury or censoring will be basic data used to calculate the time at risk, expressed in hours spent running and defined as the time scale.^14^ Participants will be right-censored if lost to follow-up or at the end of the intervention period. Average running practice characteristics will be computed for each participant over their specific period of observation. The assumption of proportional hazards will be evaluated using log-minus-log plots and Schoenfeld’s global test. First, unadjusted sHR will be estimated for shoe versions, body mass and other potential risk factors, such as running training characteristics. Subsequently, the variables with a p value <0.200 and well-established potential confounders will be included in an adjusted model to determine whether the model is improved with further adjustment. The model that best fits will be determined based on the log-likelihoods. Stratified analyses will be performed to investigate if the effect of shoe cushioning on injury risk is modified by sex, body mass (using the median value of body mass as cut-off, independently in men and women) or Body Mass Index. Finally, mediation analysis will investigate if the effect of cushioning on injury risk is partially explained by cushioning perception (and comfort).

Sensitivity analyses will first investigate the potential impact of the transition to the study shoe on the findings by excluding the participants who sustained an injury over the first 2 weeks (ie, left-truncated models). Second, depending on the participants’ compliance to the intervention (ie, use of the study shoes for each running session), we will exclude the participants who did not use the study shoes for (eg,) a minimum of 50% of their running sessions.

Exploratory analyses will investigate whether weight-bearing locomotion activities (ie, number of steps per day besides running practice) represent an independent risk factor for running-related injury, as well as whether injury risk depends on the socioeconomical status of the runners (eg, level of education, socioprofessional category, gross annual household income). All analyses will be performed using STATA/SE V.15.

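### Fine-Gray models on a running-hours scale with a fixed calendar end of follow-up bias the estimate for running volume, and the unadjusted estimates for factors strongly related to it, once competing events occur

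*Protocol article*

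**What the plan says.** The Statistics section assigns one model to shoe version, body mass and all other candidate risk factors: "subdistribution HR (sHR) with 95% CIs for the event of interest will be calculated using Fine-Gray models to account for competing risk". The dates of inclusion and of injury or censoring are "used to calculate the time at risk, expressed in hours spent running and defined as the time scale". Censoring is at loss to follow-up or at the end of the intervention, which the Data collection section sets at six months from receipt of the shoes.

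The model building begins thus: "First, unadjusted sHR will be estimated for shoe versions, body mass and other potential risk factors, such as running training characteristics". Variables with p below 0.200 and established confounders then enter an adjusted model. An exploratory analysis asks whether off-training activity ("number of steps per day besides running practice) represent an independent risk factor for running-related injury") matters. The article states no cause-specific hazard model, and it neither names the competing events nor gives their frequency. On planning, the Sample size section says: "A sample size calculation for Cox regression was used to determine the number of participants needed for the study’s primary hypothesis".

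**The concern.** Each choice is defensible alone; the difficulty lies in the combination. If follow-up lasts 26 weeks and time is counted in running hours, a runner with weekly volume w is administratively censored at about 26 × w hours. Running volume is one of the training characteristics to be tested, so for that covariate the censoring time is almost determined by the covariate.

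Fine-Gray keeps a runner who has had a competing event in the risk set and weights that runner by the chance of still being uncensored. The standard weights take this chance from one pooled curve. Here that curve is wrong for nearly every individual, and wrong in a direction tied to volume. At stake is a published statement that more running raises the injury rate per hour when it does not. The false signal would also pass the p < 0.200 screen too often.

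**Working it through.** **Planning figure first.** Inputs from the Sample size section: "With an alpha of 0.05 and a power of 80" per cent, "an average injury rate of 30" per cent, "an expected HR=1.50 between groups", equal allocation, 10% drop-out. Taking alpha as two-sided (not stated), Schoenfeld's formula for two equal arms gives 4 × (1.960 + 0.842)² / (ln 1.5)² = 191 events. Then 191 / 0.30 = 637, 637 / 0.90 = 708 for two arms, and 708 × 3/2 = 1062 for three. The stated 1068 is reproduced to within 1%. This confirms the planning of a pairwise Cox comparison and has no bearing on the defect below.

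**Mechanism.** After a competing event at hour s, the Fine-Gray weight at a later hour t is G(t)/G(s), with G the pooled censoring curve. The correct weight uses G given the runner's own volume. For illustration, assume weekly hours are lognormal with median 2.5 and log-SD 0.5, and ignore drop-out:

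- One log-SD below the median: 2.5 × e^(-0.5) = 1.52 h/week, so follow-up ends at 26 × 1.52 = 39 h.
- Median: 26 × 2.5 = 65 h.
- One log-SD above: 2.5 × e^(0.5) = 4.12 h/week, so follow-up ends at 26 × 4.12 = 107 h.

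At 65 hours the pooled G is about 0.5. After an early competing event (G(s) close to 1), both the low-volume and the high-volume runner get a weight of about 0.5. The correct weights are 0 and 1. Late risk sets therefore hold too many low-volume and too few high-volume runners with competing events, and volume looks harmful.

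**Simulation.** From the document: n = 1068, 30% injured, 10% drop-out, six-month end (26 weeks). Assumed: log-SD of weekly hours 0.5 and competing events in 5/10/15% of participants. The median of weekly hours only rescales the time axis. The injury hazard per running hour is the same for everyone, so the true cause-specific HR is 1. Each runner's true, fixed weekly volume is used. Effects are per doubling of volume, and ranges cover repeated simulations of 250 to 1000 trials per setting.

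| Competing events | 5% | 10% | 15% |
|---|---|---|---|
| Equal rate per running hour (true sHR = 1): sHR | 1.04-1.05 | 1.08-1.09 | 1.10-1.11 |
| Rejection at nominal 5% | 6-8% | 13-14% | 20-26% |
| Equal rate per calendar week: sHR | 1.08-1.09 | 1.15-1.16 | 1.22-1.24 |
| Rejection at nominal 5% | 12-14% | 35-41% | 70-73% |

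Cause-specific Cox on the same data gives HR 0.99-1.01 and about 3-8% rejection.

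The first two rows isolate the weighting error, because there the true sHR is also 1. In the last two rows, low-volume runners have more competing events per running hour. Part of that departure is a real subdistribution difference.

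**Sensitivity.** Volume was split at the median, with competing events at an equal rate per hour and log-SD 0.3/0.5/0.7 (600 trials each). At 10% competing events the sHR is 1.05/1.08/1.11 with 7/9/12% rejection; at 20% it is 1.08/1.13/1.18 with 10/15/26%. With no competing events the two models coincide (sHR 1.00-1.01, rejection 4-6%).

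**Other factors.**

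- A null factor whose carriers run 1.5 times as much, unadjusted, 5/10/20/30% competing events: sHR 1.02/1.04/1.06/1.08 with 5/5/7/12% rejection (per hour), or 1.03/1.07/1.13/1.19 with 7/8/19/34% (per calendar week). With volume added, at 2-15% competing events, the sHR is 0.99-1.01 with rejection 3-10% (200 trials per setting).
- Body mass correlated -0.25 with volume: rejection 5-9%.
- Shoe version with no effect: rejection 4-6% under both models.
- Steps, if one assumes a competing-event HR of 1.5 per SD of steps: sHR 0.95 with about 20% rejection at 15% competing events, and about 7% rejection at 5-10%.

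**Screen and adjustment.** With competing events per calendar week, a null volume effect passes p < 0.200 in 36/64/89% of trials under Fine-Gray, against 17-19% under Cox. Fitting volume and body mass together leaves the volume sHR at 1.08/1.15/1.22.

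**The case against.** The strongest reply is that the protocol speaks of injury risk and chose subdistribution hazards deliberately. It nowhere states a null of no effect per running hour among those still running, so preferring a cause-specific hazard is partly a choice of estimand. This stands for the calendar-week rows: a reader might infer that all of the roughly 70% rejection is false, and the document does not support that. It does not dispose of the per-hour rows, where the estimator misses its own target.

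Second, the size depends on competing-event frequency and spread of volume, which the article does not give and a fuller document may. This also stands. At 2% competing events the volume sHR is 1.01-1.03 with 4-8% rejection.

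Third, the adjusted model is where an independent risk factor is judged, and adding volume removes the distortion for factors that act only through volume. That is correct. It does not help volume itself or the planned unadjusted sHRs.

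Fourth, the Objectives list no question on average volume; the training question there concerns acute changes in load and is exploratory. This limits the importance of the point, although the Abstract includes the association of training with injury risk among the planned analyses.

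A reader might go further and infer that the shoe result, or every risk-factor result, is invalid. The checks do not support that: null shoe comparisons reject at the nominal rate and body mass is close to it. Nor does a Cox sample size beside a Fine-Gray analysis demonstrate an error.

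**Conclusion.** The point holds in a limited form. For running volume, the planned model, time scale and censoring rule together give a biased sHR whenever competing events occur, even if volume affects neither injury nor competing events per hour. The same applies, more weakly, to unadjusted sHRs of factors strongly related to volume. At 10% competing events the bias for volume is about 8% per doubling, and the false-positive rate is between two and three times nominal. At 5% or below, in the per-hour case, it is small.

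These sizes rest on the assumed spread of weekly hours and competing-event frequencies; the direction does not. That competing events arise per calendar week is a further assumption, and so is any effect of steps on them, which the exploratory steps question would need before it is affected. The change is worth making before analysis, but nothing here threatens the primary comparison.

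**What to change.** In the Statistics section, estimate the effects of running training characteristics and other non-randomised risk factors, including off-training steps in the exploratory analyses, with cause-specific Cox models on the running-hours scale, censoring at the competing event. Include weekly running volume in the models for the other factors in every case, without leaving it to the p-value screen.

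Keep the Fine-Gray sHR for the shoe comparison. For risk factors, keep it only as a supplement describing cumulative incidence, and state that a volume-related sHR is not to be read as an effect on injury per running hour.

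The cost is a change of wording and one extra model in the same software on the same data. The drawback is that cause-specific HRs do not translate directly into cumulative incidence, so incidence curves should still be shown.

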### Intervention

The study shoes are prototypes derived from a model available on the market (Kiprun KS 500 2) and will be anonymised for the purpose of this trial. The soles of the shoes will be customised for the study. The three running shoe versions will have the same design, except for their cushioning properties at the rear and forepart of the shoe, which will differ by about 40% and 30%, respectively (figure 2). Nevertheless, cushioning properties will remain within the range of values of the shoes available on the market (linear equivalent stiffness: 40±5 to 60±5 and 60±5 to 80±5 N/mm, at the rear and forepart of the shoe, respectively). We expect a difference in shoe weight lower than 30 g between the three versions (for size 43). The difference in cushioning properties between shoe versions will be created by modifying the type of foam and the foaming process. A set of shoes (5 pairs per version, shoe size 43) will be tested for stiffness properties by the manufacturer according to a standardised protocol (Impact test: ASTM F1614, Procedure A)^26^ to provide accurate data on the technical specifications (stiffness and dissipated energy). The cushioning properties (linear equivalent stiffness) of the study shoe versions will be characterised as follows (see also figure 2): hard shoe version (‘Hard-Hard’—about 60±5 and 80±5 N/mm at the rear and forepart of the shoe, respectively), mixed shoe version (‘Soft-Hard’—about 40±5 and 80±5 N/mm) and soft shoe version (‘Soft-Soft’—about 40±5 and 60±5 N/mm). The main hypothesis will be tested by comparing the mixed shoe version with the hard shoe version, while the secondary hypothesis will be tested by comparing the soft shoe version with both the hard and mixed shoe versions.

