### Stratified randomisation

Participants will be randomised at a 1:1:1 ratio to one of the three treatment arms. A block randomisation (block size 12) will be performed. Randomisation will be stratified by sex, as the latter influences body mass. Based on data from previous studies, the study population is expected to include about 40% of women. A statistician (at Luxembourg Institute of Health) who is not involved in any other part of the study will provide two pre-established randomisation lists before the beginning of recruitment. The participant identification number will comprise of four digits: the first digit corresponding to the participant’s sex (1=female, 2=male), followed by three digits corresponding to the randomisation number. The study groups and shoes will be coded, and an IT developer will upload the randomisation lists to the data collection system. Then, the data collection system will provide the investigator in charge of the recruitment with a study group number for each participant, according to the randomisation lists. The investigator will upload the shoe number according to the shoe size chosen and study arm so that the electronic system will perform cross-validation. The investigators in charge of the recruitment, the follow-up and data quality check, and the participants will be blinded regarding the shoe version distributed. The shoe code will be broken after the completion of data analysis.

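### The randomised shoe effect is put through a risk-factor model search (p<0.200 screen, then best log-likelihood) whose candidates include training variables measured after randomisation

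*Protocol article*

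**What the plan says.** The primary contrast is clear. Under Intervention: "The main hypothesis will be tested by comparing the mixed shoe version with the hard shoe version". Under Stratified randomisation: "Participants will be randomised at a 1:1:1 ratio to one of the three treatment arms", and "Randomisation will be stratified by sex, as the latter influences body mass".

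The Statistics section then sets out a single strategy for the shoe, body mass and other risk factors, using Fine-Gray models with hours of running as the time scale:

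- Step 1: "First, unadjusted sHR will be estimated for shoe versions, body mass and other potential risk factors, such as running training characteristics".
- Step 2: "the variables with a p value <0.200 and well-established potential confounders will be included in an adjusted model", to see whether adjustment improves the model.
- Step 3: "The model that best fits will be determined based on the log-likelihoods".

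The same section says that running-practice variables are averaged for each participant over that participant's own time under observation. No sentence holds shoe version in the adjusted model, names sex as a fixed covariate, or separates the model for the randomised contrast from the models for the risk factors.

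**The concern.** Univariate screening followed by a search for the best fit is a common way to build a risk-factor model in a cohort. Here the same steps are applied to a randomised contrast, and two things follow.

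First, training averages over follow-up are consequences of what happens after the shoe is handed over. If the shoe alters how much or how hard people run, or causes minor complaints that make them cut back, conditioning on those averages breaks the comparison that randomisation protects. It may remove part of a real effect or create an apparent one.

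Second, the adjusted shoe estimate depends on which covariates the data happen to select. The confirmatory result would then rest on a model that nobody could have written down before the data were seen.

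**Working it through.** **1. The design figure.** Inputs from Sample size: alpha 0.05 (taken as two-sided), power 80%, injury rate 30%, drop-out 10%, and "an expected HR=1.50 between groups, 33% of participants randomised to each shoe group". For one 1:1 comparison by Schoenfeld's formula:

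- events = 4 × (1.960 + 0.842)² / (ln 1.5)² ≈ 191
- participants in two arms = 191 / 0.30 ≈ 637
- with drop-out = 637 / 0.90 ≈ 708, or 354 per arm
- three arms = 1062, against 1068 stated (0.6% apart)

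At the stated size, expected events in the two arms are 712 × 0.9 × 0.30 = 192, with power 80.3%. The planned size thus matches a single two-arm comparison without covariates. Fixing the model in advance does not disturb it.

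**2. When the candidates are measured.** Putting the sections side by side:

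- Statistics: training averages run over the observation period, so they start after shoe receipt and stop at injury or censoring.
- Study outcomes: the primary event needs a restriction of at least 7 days. A shorter complaint that limits distance, speed or duration is not a primary event, but it lowers the training average while the runner is still at risk.
- Objectives: acute changes in training load are to be studied as a cause of injury.
- Statistics: a mediation analysis through cushioning perception and comfort is planned, so the authors already consider that the shoe may act through variables measured after randomisation.

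Training averages therefore cannot be treated as baseline covariates.

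**3. Illustration under no true shoe effect.** Assumptions, none from the document: two arms of 320 and a Cox model without competing events; a latent trait that raises injury hazard (log HR 0.5 per SD) and lowers log weekly volume by 0.3 per SD; further log-volume noise with SD 0.3; 2.5 hours a week for 26 weeks; baseline hazard 0.0047 per hour; 2000 runs. In the selected model, volume is added when its own p is below 0.200.

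| Shoe effect on volume | Unadjusted HR | Rejection | Selected-model HR | Rejection |
|---|---|---|---|---|
| 0% | 1.00 | 4.5% | 1.00 | 4.7% |
| 5% | 1.01 | 4.5% | 1.04 | 5.6% |
| 10% | 1.02 | 5.7% | 1.08 | 8.6% |
| 20% | 1.04 | 5.3% | 1.16 | 16.9% |

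Volume passed the screen in 99 to 100% of runs. The Monte Carlo standard error of a 5% rejection rate is √(0.05 × 0.95 / 2000) ≈ 0.5 percentage points. The 5% row is therefore not clearly inflated, whereas the 10% and 20% rows are. With a true HR of 1.5 and no shoe effect on volume, the unadjusted and selected HRs were 1.47 and 1.48, so selection did no visible damage there.

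**4. Illustration with a true shoe effect acting through discomfort.** Assumptions, again not from the document: 640 runners; discomfort in 60% against 20% by arm; hazard multiplied by 2.6 with discomfort; volume cut by 30 to 50%; 150 replicates. Adding average volume moved the shoe HR from 1.44 to 1.41 in one setting and from 1.37 to 1.29 in another, towards no effect.

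Together, the two illustrations show that the bias can run either way.

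**The case against.** Several points on the other side have force.

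- *An unselected estimate exists.* Step 1 yields an unadjusted shoe sHR in every case, so a reader who infers that the shoe effect can come only from the selected model goes too far. This stands. What remains is that the text goes on to pick a best model and does not say that the unadjusted estimate is the one that counts.
- *Shoe version is probably meant to stay in.* A reader might infer that the randomised factor will be dropped whenever its p is 0.200 or more. The wording allows this, but the stated purpose of seeing whether more adjustment helps suggests covariates added to a shoe model, and the later stratified and mediation analyses need the shoe as exposure. The chance of failing the screen can be calculated, but it does not measure harm: the unadjusted estimate would still be there, and a contrast with p of 0.200 or more is already non-significant.
- *Log-likelihood may be shorthand.* Raw log-likelihood cannot fall as terms are added, so a reader might infer that the largest model always wins. The phrase may equally mean likelihood-ratio tests or an information criterion. Fine-Gray models are fitted by a pseudo-likelihood, so such tests are not standard, but this is a secondary point.
- *The shoe may not change training.* Participants are blinded and are told to keep to their usual or planned training. That makes a large effect on volume less likely without excluding it.
- *Blinding limits steering.* The shoe code is broken only after the analysis is complete. This guards against deliberate choice of a model, but not against a model that depends on the data.
- *The paragraph also serves the risk-factor aims.* For those the recipe is common practice, and baseline prognostic adjustment can help a randomised comparison. Both are compatible with a separate, fixed model for the shoe effect.

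Nor is this simply detail left to an analysis plan: the article states a specific rule, and that rule is unsuitable for the randomised contrast.

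**Conclusion.** The point holds in this form: as written, one data-driven recipe covers the randomised comparison and the risk factors, and following it can adjust the shoe effect for variables measured after randomisation. This should be fixed, but it does not undermine the design.

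The size cannot be derived from the document. Under the assumptions shown, the bias runs from none (shoe does not alter training) to a spurious HR of 1.16 with 16.9% false rejections (shoe changes volume by 20%), and a true effect may be modestly diluted. A claim that adjustment always shrinks the effect, or that the shoe term will be screened out, is not supported.

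**What to change.** State in the Statistics section that:

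- the primary analysis is mixed versus hard, from one Fine-Gray model fixed in advance;
- shoe version is in every model for the shoe effect, whatever its p value;
- adjustment is only for sex, as stratification factor, and a short named list of baseline variables already collected, such as body mass and previous injury;
- no variable measured after shoe receipt enters a treatment-effect model;
- the p<0.200 screen, the log-likelihood choice and the training averages are confined to separate risk-factor models labelled exploratory.

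The unadjusted sHR can be kept as a supporting result. The cost is wording only: sample size and power stay as they are. The one small downside is that the covariate list must be chosen now.
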